# A randomized, parallel control and multicenter clinical trial of evidence-based traditional Chinese medicine massage treatment VS External Diclofenac Diethylamine Emulgel for the treatment of knee osteoarthritis

**DOI:** 10.1186/s13063-022-06388-5

**Published:** 2022-07-08

**Keywords:** Clinical effect, Safety evaluation, Evidence-based traditional Chinese medicine massage, External Diclofenac Diethylamine Emulgel, Knee Osteoarthritis, Magnetic resonance imaging, Multi-center, Clinical trial

## Abstract

**Background:**

Both massage and topically administered NSAIDs are safe and effective treatments for knee osteoarthritis (KOA); however, different massage technique sects in China caused assessment difficulties for the treatment of KOA. In order to standardize the massage techniques and procedures, we organized multi-disciplinary experts in China to acquire an evidence-based traditional Chinese medicine massage treatment of knee osteoarthritis. The purposes of this study will be to provide clinicians a complementary and alternative therapy for patients and to evaluate the efficacy and safety of evidence-based traditional Chinese medicine massage treatment of KOA compared to External Diclofenac Diethylamine Emulgel.

**Methods and design:**

A randomized controlled trial in which 300 participants diagnosed with KOA will be recruited and randomly allocated to either the experimental group or the control group in a ratio of 2:1. Two hundred participants will receive evidence-based traditional Chinese medicine massage 2 sessions per week for 10 weeks as the experimental group, and 100 participants will receive External Diclofenac Diethylamine Emulgel 3–4 times per day for 10 weeks as the control group. The patients in the two groups will receive follow-up at two time points at 5 weeks and 10 weeks from the beginning of treatment, respectively. The MRI scans and X-ray will be performed at baseline and at the end of the intervention. The primary outcome will be the changes in the Western Ontario and McMaster Osteoarthritis Index (WOMAC). Secondary outcomes will be measured by the PRO scale for knee osteoarthritis based on the concept of traditional Chinese medicine (Chinese scale for knee osteoarthritis (CSKO)), X-ray evaluation, and MRI scan evaluation. The data of WOMAC and CSKO will be analyzed at the baseline, 5 weeks, and 10 weeks from the beginning of treatment. The data from MRI scans and X-rays will be analyzed at baseline and at the end of the intervention. The significance level sets as 5%. The safety of interventions will be evaluated after each treatment session.

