### Informed consent and participant safety

Participants will be required to sign an informed consent and have the same chance to receive appropriate treatment. The safety of participants will be monitored in every visit. Two attending physicians and two responsible joint care specialists will be responsible for the collaboration and guidance of clinicians during each clinical trial and implementation. The two chief joint surgeons constitute the endpoints Adjudication Committee, which is responsible for the overall supervision of the clinical trials.

During the treatment, any adverse events, such as local skin dryness, skin irritation, fracture, dislocation, or increased pain should be recorded and reported to the relevant responsible unit and the ethics committee in time. If the adverse events such as death, fractures, and organs injury are confirmed to be related to the study, the Ethics Committee of Guang’anmen Hospital, China Academy of Chinese Medical Sciences, has the right to discontinue or modify allocated interventions. If an adverse event occurs during the clinical trial, medical experts will be engaged to assess and investigate the actual cause, and medical and financial compensation will be made to participants. If the participants cannot tolerate these adverse reactions, treatment will be discontinued and the participants will be withdrawn from the study.

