### Interventions

#### Experimental group

Two hundred patients in the experimental group will receive 20 sessions of manual massage treatment (2 sessions weekly for 10 weeks,10 min one session). Use the definite evidence-based traditional Chinese medicine massage technique for knee osteoarthritis to do the massage treatment [10].

During the treatment period, other Chinese and Western drugs and treatment methods (including physical therapy and psychotherapy, etc.) for knee osteoarthritis are not used. In cases of intolerable knee pain, the patients will be instructed to take loxoprofen sodium tablets (60 mg, oral 3/day) as a rescue medication. The use of other treatments, such as injections of any kind, moxibustion, acupuncture, or cupping, will not be allowed.

When combined with other diseases, the drugs and treatments must be continued, and the drugs and treatments need to be recorded in detail in the combined medication list.

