#### Control group

One hundred patients in the control group will receive External Diclofenac Diethylamine Emulgel (Beijing Novartis Pharma Ltd. producing, trade name: Vitalin Emulgel) treatment (3–4 times per day for 10 weeks). Other interventions will be similar to the experimental group.

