### Safety outcomes

(1) Vital signs: body temperature, resting heart rate, respiratory, and blood pressure after 10 min of rest (systolic blood pressure, diastolic blood pressure). (2) Laboratory examination: blood routine (RBC, WBC, platelet, hemoglobin), urine routines (urine red cell, LEU, urinary protein, glycated hemoglobin alc), stool routine+occult blood, and liver function (ALT, AST), and renal function (BUN, Cr, 12 lead routine electrocardiogram). (3) Manipulation-related adverse events, such as ecchymosis, subcutaneous hemorrhage, fracture, and dislocation. (4) Drug-related adverse events, such as gastrointestinal tract response. (5) Other adverse events.

The safety of each therapy was evaluated by comparing the changes in blood and urine routine, liver and kidney function, electrocardiography before and after the treatment, and the incidence of adverse events during the treatment.

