### Statistical analysis

All statistical analyses will be performed with the SPSS software (SPSS 20.0, SPSS Inc., Chicago, IL, USA) by statisticians who are independent of the research team and blinded to the group allocation. Data analysis will be based on the intention-to-treat (ITT) principles. All numerical data will be presented as the mean ± SD, and categorical variables will be described with percentages (%). All the statistical tests are bilateral inspection; *p* < 0.05 is considered statistically significant. Paired *t* test or the paired rank sum test is used for the comparison within the groups; the *χ*^2^ test or Fisher’s exact probability method is used for the count data, and the Wilcoxon rank sum test is used for the rank data between groups. CMH *χ*^2^ test is used for the primary outcome of WOMAC improve rate. It is necessary to adjust the baseline and centers of the changes in WOMAC score between the groups with the covariance method.

The secondary outcome includes CSKO score, X-ray data, and MRI data, which are all measurement data, and a group *t*-test or the Wilcoxon rank-sum test is used for comparison between the groups. The *χ*^2^ test or Fisher’s exact probability method is used for participants’ dropout and adverse events rate analysis.

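### Adverse events are likely to be captured more fully with massage (20 sessions) than with gel (two stated follow-ups), yet the planned test compares the unadjusted rates

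*Protocol article*

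**What the plan says.** The abstract of the protocol article ties safety assessment to treatment sessions: "The safety of interventions will be evaluated after each treatment session". The section on informed consent and participant safety ties it to attendance: "The safety of participants will be monitored in every visit". That section also requires any adverse event during treatment to be recorded and reported.

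The two arms attend on different schedules. Massage patients "will receive 20 sessions of manual massage treatment", two a week for ten weeks. Under Control group, the gel is given as "treatment (3–4 times per day for 10 weeks", with no session or clinic contact defined. The contacts common to both arms are these: "The patients in the two groups will receive follow-up at two time points at 5 weeks and 10 weeks from the beginning of treatment".

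Safety outcomes then names "the incidence of adverse events during the treatment" as a basis for judging each therapy, and Statistical analysis assigns a chi-square or Fisher exact test to "dropout and adverse events rate analysis". No allowance for the number of contacts is described.

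**The concern.** Comparing safety is part of the main purpose stated under Methods and design. A raw incidence comparison is fair only if an event of a given kind has about the same chance of being recorded in either arm. Here a massage patient meets study staff who assess safety about twice a week. A gel patient, on the stated schedule, is asked twice in ten weeks.

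Several of the events that the article names are mild and usually pass: skin dryness, skin irritation, ecchymosis, increased pain. Whether they are recorded plausibly depends on how soon someone asks. The Introduction says that local skin reactions are more common with topical NSAIDs, so the harm expected with the gel falls in the arm that is asked least often.

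Two errors could follow: a false excess of adverse events with massage, or a real gel excess that disappears.

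**Working it through.** The article gives no expected adverse-event rate and no power for safety, so there is no figure of its own to reproduce. Its sample size concerns efficacy only.

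**Scheduled safety contacts after baseline**
- Massage: 2 per week × 10 weeks = 20 sessions. The week 5 and week 10 follow-ups may coincide with sessions, so the total is 20 to 22.
- Gel: 2 (weeks 5 and 10).
- Ratio: 20/2 = 10, so about 10 to 1.

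**Effect on the planned test**

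Inputs from the article: 200 massage and 100 gel patients (Sample size); two-sided 5% level (Statistical analysis). Inputs assumed: the true risk r, equal in both arms, and the share of events captured in each arm, c.

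The expected observed rate in an arm is r × c. With x events in 200 and y in 100, and p = (x + y)/300, the uncorrected chi-square rejects when |x/200 − y/100| / √[p(1 − p)(1/200 + 1/100)] exceeds 1.96. The rejection probability is the sum of the two binomial probabilities over all (x, y) that reject (exact enumeration).

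For r = 20% and 95% capture with massage (0.20 × 0.95 = 19%):

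| Gel capture | Expected gel rate | False rejection |
|---|---|---|
| 80% | 16% | 9% |
| 70% | 14% | 18% |
| 60% | 12% | 33% |
| 50% | 10% | 53% |

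Rough check of the 60% row: 38/200 against 12/100 gives p = 50/300 = 0.167, standard error 0.0456 and z = 0.07/0.0456 = 1.53. Then Φ(1.53 − 1.96) = Φ(−0.43) ≈ 0.33.

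Over the same range of gel capture, false rejection is 6% to 25% at r = 10% and 13% to 76% at r = 30%. With equal, complete capture in both arms it is about 5% at all three risks.

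**An extreme case: 14-day events, no recall at all**

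Suppose that an event is recorded only if it is present at a contact, and that onset is uniform over 70 days. With gel contacts on days 35 and 70, the share caught is (14 + 14)/70 = 40%, so the expected rate is 20% × 0.40 = 8%. If the last massage session is on day 68, only events starting after it are missed: 20% × 68/70 = 19.4%. The exact rejection probability for 19.4% against 8% is about 77%.

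**Masking**

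Suppose that the true risks are 12% with massage and 20% with gel, with 95% and 60% capture. The expected observed rates are 0.12 × 0.95 = 11.4% and 0.20 × 0.60 = 12.0%, so the true 8-point difference almost vanishes.

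**The case against.** The best case on the other side has four parts.

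- **Common data collection.** Under Data management and monitoring, the outcome assessors, who are blinded to allocation, collect adverse events on case report forms. If they do so only at the common visits, the analysed data might come from the same people and times in both arms. This does not settle the matter. The article does not limit adverse-event data to those visits, and the participant-safety section requires any event during treatment to be recorded, which includes events found at a session.

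- **Contacts that are not visible.** Fig. 1, the assessment schedule, is not shown, and Trial conduct mentions records of drug receipt, distribution and return. Further gel contacts are possible. None is scheduled in the text or named as a safety assessment, and the text gives only weeks 5 and 10. The point therefore holds for the article as written.

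- **The no-recall model is not the protocol's rule.** This stands. Safety outcomes compares incidence over the whole treatment period, not the events present on two days, so 19.4% against 8% marks an extreme. With half of the missed 14-day events recalled, the gel rate would be 8% + 0.5 × (20% − 8%) = 14%, and 19.4% against 14% rejects about 20% of the time.

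- **No safety conclusion would survive.** A reader might infer this, but the documents do not support it. The extra contacts work against massage, so a finding that massage shows no more adverse events than gel would be conservative. Laboratory tests and ECG are compared before and after treatment, and fracture, dislocation or organ injury hardly depend on being asked about.

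**Conclusion.** The point holds for one component of the safety evaluation, the between-arm comparison of adverse-event incidence, and mainly for mild and transient events. On the stated schedule, contacts differ by about 10 to 1 and the test ignores this. The likely direction is against massage: an apparent massage excess would be ambiguous, and a real excess of skin reactions with gel could be hidden.

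The size cannot be derived from the article. With an assumed true risk of 20% in both arms, 95% capture with massage and 60% with gel, false rejection is about 33% instead of 5%. Across gel capture of 50% to 80% it runs from 53% down to 9%. The 77% figure needs 14-day events and no recall at all, and should not be read as the expected case. The primary outcome is not affected.

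**What to change.** Base the between-arm adverse-event test on events elicited by the same structured checklist at weeks 5 and 10 in both arms, each time covering the whole interval since the previous assessment. Ask it after WOMAC and CSKO have been completed, so that the answers do not reveal the allocation to the assessor before those scores are taken.

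Report all adverse events, including those found at massage sessions, by arm in a second, descriptive table that states the difference in contacts. Leave per-session safety monitoring unchanged. If the full protocol already sets a common adverse-event schedule for the gel arm, the article and analysis plan need only say so and name it as the source for the test.

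The cost is one checklist at visits that already exist and a few lines in the analysis plan. The checklist itself has to be in use during data collection, because later analysis cannot recover gel events that nobody asked about. The downside is that recall over five weeks loses some mild events in both arms, and patients questioned at 20 sessions may still remember more, so some difference in recall may remain.

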**Discussion:**

This study will provide clinicians with much-needed knowledge for the treatment of KOA through a controlled trial.

**Trial registration:**

Chinese Clinical Trial Registry ChiCTR1800014400. Registered on 10 January 2018

## Introduction

Knee osteoarthritis (KOA) ranks highly among global causes of disability and chronic pain, particularly in people over 50 years of age [1]. Structured exercise programs, dietary weight management, and mind-body exercise (such as tai chi and yoga) were considered by the panel to be effective and safe for all patients with knee OA [2–5]. These updated OARSI guidelines recommended non-pharmacological as the core treatments for KOA in all cases [6].

Massage is a safe and non-pharmacological treatment with limited contraindications and no known serious adverse events [7]. Traditional Chinese massage has a positive effect on KOA and widely used in China. In recent several studies have shown that Chinese massage therapy decreased pain and may improve extensor muscle strength, and it may improve walking ability for these KOA patients; however, different massage sects in China caused assessment difficulties for the treatment of KOA [8, 9]. In order to standardize massage techniques and procedures, we organized multi-disciplinary experts in China to conduct a questionnaire survey and field discussions and successfully acquire an evidence-based traditional Chinese medicine massage treatment of knee osteoarthritis [10].

Topically administered non-steroidal anti-inflammatory drugs (NSAIDs) such as Diclofenac solution attained significantly greater improvement in pain reduction in patients with KOA and are widely used in the world [11–14]. However, local skin reactions happened more commonly in patients treated with topical NSAIDs [15].

In order to provide clinicians a complementary and alternative therapy for patients with KOA, and to determine whether evidence-based traditional Chinese medicine massage is a safe and effective therapy, we design and conduct the trial. Compared to topical NSAIDs (e.g., Diclofenac Emugel), which is strongly recommended (level 1a), massage is conditionally (level 3) recommended by the OARSI guidelines [6]. In the trial, we hypothesized that the evidence-based traditional Chinese medicine massage group would be non-inferior to the External Diclofenac Diethylamine Emulgel group in the treatment for KOA. In order to enhance the reliability of evidence-based traditional Chinese medicine massage in the treatment of KOA, we take the External Diclofenac Diethylamine Emulgel as the control group to evaluate the efficacy and safety in the study. In the overall design of the experiment, this scheme has randomization, control, and multi-center clinical trial.

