## Methods and design

The main purpose of this study is to compare the safety and efficacy of evidence-based traditional Chinese medicine massage and External Diclofenac Diethylamine Emulgel in KOA patients. Three hundred participants will be recruited for the study. Clinical data measurements, X-rays, and MRI scans will be evaluated at baseline and the end of treatment (Fig. 1). The study has been approved by the ethical committees of Guang’anmen Hospital (NO:201-135-KY-1) and registered in the Chinese Clinical Trial Registry (http://www.chictr.org.cn/showproj.aspx?proj=24457). The registration number is ChiCTR1800014400. The protocol will be reported following Standard Protocol Items: Recommendations for Interventional Trials (SPIRIT) statement.

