### Sample size

According to the literature, the average effective rate of treating knee osteoarthritis only through massage is 95.6% and 79.8% by application of external diclofenac diethylamine emulsion latex [15]. According to the sample size calculation formula, the minimum sample size of each group is *n* = 85.49. Considering expulsion case and getting significant results, at the same time, in order to implement layered research in the experimental group, we planned the ratio of the cases in the experimental group and the control group is 2:1, and the number of included cases was 300. There were 200 cases in the experimental group, and 100 cases were in the control group.

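### The hypothesis is non-inferiority, but the sample size is a superiority calculation and the tests have no margin, so only a significant win for massage could support the hypothesis

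*Protocol article*

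**What the plan says.** **Hypothesis.** The Introduction of the protocol article states: "we hypothesized that the evidence-based traditional Chinese medicine massage group would be non-inferior to the External Diclofenac Diethylamine Emulgel group". Non-inferiority is not mentioned again. The opening of Methods and design is neutral: "The main purpose of this study is to compare the safety and efficacy of evidence-based traditional Chinese medicine massage".

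**Sample size.** The planning rates are given as "the average effective rate of treating knee osteoarthritis only through massage is 95.6% and 79.8% by application of external diclofenac diethylamine emulsion latex". The section then reports a minimum of 85.49 per group ("According to the sample size calculation formula, the minimum sample size of each group is"). It enlarges this to 300 at 2:1 to allow for withdrawals, to obtain significant results and to permit stratified work in the massage arm: "There were 200 cases in the experimental group, and 100 cases were in the control group". It states no power, margin or dropout rate.

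**Analysis.** "All the statistical tests are bilateral inspection", with p < 0.05 as the threshold. The WOMAC improvement rate gets a CMH chi-square test. The change in WOMAC score is compared by a covariance method adjusting for baseline and centre. The Outcomes section makes week 10 the final evaluation.

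**The concern.** The article states a hypothesis, a sample-size derivation and a testing rule, and the last two do not belong to the first. A non-inferiority hypothesis needs a margin, a confidence limit (or equivalent test) set against that margin, and a sample size derived from it. The plan instead has an expected advantage for massage and tests of no difference.

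What is at stake is what the trial may conclude. A significant advantage for massage would settle the matter. A non-significant difference would not, because p > 0.05 is not evidence of non-inferiority. The Introduction itself reports that the comparator carries a strong guideline recommendation and massage only a conditional one, so an unsupported claim that massage is no worse would matter to clinicians. Because the power depends on the margin, a margin chosen after results by arm were known could decide the outcome.

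**Working it through.** **1. Reproducing the plan's figure**

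Inputs from Sample size: p1 = 0.956 (massage), p2 = 0.798 (diclofenac), difference 0.158. Two-sided alpha of 0.05 comes from the Abstract and Statistical analysis. Power is not stated; 90% is inferred from the match below.

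Superiority formula, 1:1, unpooled variance: n = f × [p1(1 − p1) + p2(1 − p2)] / (p1 − p2)², with f = (1.96 + 1.28)² ≈ 10.5.

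- p1(1 − p1) = 0.956 × 0.044 = 0.04206
- p2(1 − p2) = 0.798 × 0.202 = 0.16120
- Sum = 0.20326; 0.158² = 0.024964
- n = 10.5 × 0.20326 / 0.024964 = **85.49**, the stated figure to two decimals. Unrounded normal quantiles give 85.55.

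No margin enters this formula. Other superiority variants at 90% power do not match: 90.8 with pooled variance, 88.7 with the Fleiss form, 80.9 with arcsine.

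**2. When the written rule can establish non-inferiority**

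A two-sided p < 0.05 in favour of massage puts the whole 95% interval above zero, which implies non-inferiority for any margin. With 200/100 patients this happens in:

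- about 2.5% of trials if the true rates are equal (the upper half of a two-sided 5% test)
- about 18% if massage is truly 5 points better than 79.8%
- about 96% (unpooled variance) to 98% (pooled variance) at the plan's own rates of 95.6% and 79.8%.

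In all other trials the plan has no rule for the stated hypothesis. Two assumed deficits show why a non-significant result cannot fill the gap. If massage is truly 10 points worse (69.8% against 79.8%), p > 0.05 still occurs in about 51% of trials (55% with pooled variance). If it is truly 5 points worse, it occurs in about 83%.

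**3. Non-inferiority power of 200/100**

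The documents give no margin, so this is a range under assumptions: equal true rates of 79.8%, one-sided 2.5% (the lower limit of a two-sided 95% interval), no dropout.

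SE = √[0.798 × 0.202 × (1/200 + 1/100)] = 0.0492; power = Φ(margin/SE − 1.96).

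| Assumed margin | margin/SE − 1.96 | Power |
|---|---|---|
| 5 points | −0.94 | 17% |
| 10 points | 0.07 | 53% |
| 15 points | 1.09 | 86% |
| 20 points | 2.11 | 98% |

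The smallest margin supported is (1.96 + 0.84) × 0.0492 = 13.8 points at 80% power and (1.96 + 1.28) × 0.0492 = 15.9 points at 90%. If massage really is 15.8 points better, as Sample size assumes, non-inferiority power exceeds 99% for any margin of 5 points or more.

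**The case against.** The strongest case on the other side has five parts.

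- **The plan is not powerless.** A reader might infer that it cannot answer its own question, or that 200/100 carries no power for non-inferiority. Neither follows. A significant result for massage answers the question and is about 96–98% likely at the plan's own rates. Non-inferiority power ranges from low to high according to the margin. This stands, and it limits the point to the case where superiority is not shown.
- **Two-sided testing is not the defect.** The lower limit of a two-sided 95% interval carries the usual 2.5% error for a non-inferiority claim, and the planned covariance analysis would yield such an interval. This stands. What is missing is the margin and the rule that uses it.
- **Intention-to-treat alone.** A reader might infer that it biases the trial towards non-inferiority. The documents do not support that: the direction depends on adherence, rescue use and missing-data handling. A supporting per-protocol set is also commonly left to the full protocol or SAP.
- **Misreading is conjecture.** Nothing says a non-significant result will be reported as non-inferiority. That is so. The 51% and 83% figures show only that such a result would be uninformative.
- **The margin may be in an unseen document, or behind 85.49.** A non-inferiority formula with a 20-point margin, equal 79.8% rates and 90% power gives 84.7 per group, which is close. But no such margin is stated, and the superiority formula matches to two decimals. The objection fails because the article prints a complete sizing argument of a different kind from its hypothesis; this is a contradiction, not an omission.

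**Conclusion.** The point holds. The stated hypothesis is non-inferiority; the sample size and tests are those of a superiority trial. Non-inferiority can be concluded only through a significant advantage for massage, and every other result is left without a rule. The sizing match is arithmetic on the plan's own rates, with only the 90% power inferred. The power range rests on assumed margins, equal true rates of 79.8% and no dropout.

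It would be too strong to say that 300 patients are too few. Whether they suffice depends on the margin and on the true difference, and the plan states no margin. The text must be corrected before analysis, because it determines what the trial may claim.

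**What to change.** Choose one of two routes.

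**(a) Superiority.** Change the hypothesis in the Introduction to superiority. Sample size and Statistical analysis already support it. State the power used.

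**(b) Non-inferiority.**
- Name one week-10 primary measure for the decision: either the WOMAC response rate used in Sample size, or the baseline- and centre-adjusted WOMAC change in Statistical analysis. Say what role the other keeps.
- Fix and justify a numerical margin on that measure before any comparison by arm.
- Declare non-inferiority only if the lower limit of the two-sided 95% confidence interval for massage minus diclofenac, signed so that positive values favour massage, lies above minus the margin. Test superiority afterwards at the same alpha.
- In Sample size, replace the superiority argument with the non-inferiority power that 200/100 gives for that margin.
- A supporting per-protocol analysis is optional.

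**Cost.** Either route is a change of wording and leaves data collection as it is. Under (b) the stated power may become less favourable: at equal rates, a 10-point margin would give only about 53%. The Trial status section puts the first inclusion at 1 June 2018 and predicts completed recruitment by September 2021. A margin set now must therefore be documented as chosen blind to results by arm. Route (a) avoids having to set a margin late.
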